#### Clinical outcomes

The clinical status of veterans participating in the study will be assessed at baseline, 3, and 6 months post randomization. The baseline assessment will be conducted prior to beginning CBT treatment. Assessments will be administered over the phone by a trained staff using a computer-assisted telephone interviewing system. The follow-up outcome assessments will include both generic measures applicable to all patients and disorder-specific measures.

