### Aim 2: hybrid type III study

Our second aim we will be to use a hybrid type III [35] study design to conduct an RCT comparing the effect of a modified CALM tool versus that of a manualized version of CALM on our primary outcome—CBOC mental health provider fidelity to CBT. A hybrid III study design was used given (a) a substantial and clear evidence base indicating improved clinical outcomes associated with patients receiving CALM; (b) a strong need to identify optimal delivery methods for implementing CBT in VA CBOCs; and (c) the fact that CALM has significant “implementation momentum” [35] as our VA Central Office research partners are interested in adapting the CALM tool for use in VA CBOCs. Mental health providers will be randomized to receive CBT training plus the CALM tool or a manualized version of CALM. We hypothesize that providers randomized to receive CBT training and the CALM tool will demonstrate higher treatment fidelity than providers receiving the manual. We also hypothesize that veteran patients of providers randomized to receive CBT training and the CALM tool will have clinical outcomes superior to veteran patients of providers who receive the manual.

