### Study participants

Participants will include mental health providers and veteran patients. We will recruit 34 mental health providers (all disciplines eligible) to receive training in CBT. Upon completion of training, each mental health provider will invite ten of his/her patients to participate in CBT treatment (Table 1).

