### Training and consultation

All providers will receive training in CBT. The training will be of the same length and format (3-day, face-to-face) as initial training programs in VA rollouts of EBPs [37]. The training will differ across the two groups (those randomized to receive the CALM tool versus manual) in that the final 2 h of each day will involve practice with either delivery method. All providers who complete the training (regardless of randomization) will receive consultation for 3 months, which will consist of small group discussion with “audit and feedback” reports to therapists. Consultation will focus on coaching and giving providers feedback on the delivery of CBT. Both elements have been shown to be important in ensuring proficient delivery of EBPs [38]. Providers will audiotape all of their clinical sessions, and the consultant will review a sample of audiotapes from their sessions during the first 3 months. The consultant will review all recordings from the providers’ first patient and will provide written (via e-mail) or oral (via telephone) feedback after the second and last sessions. If a provider appears to need additional instruction, the supervisor will provide weekly individual consultation over the telephone for the provider until both agree that any problems have been resolved.

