#### Fidelity ratings

Fidelity assessments will focus on therapy sessions delivered early and late in the project. Fidelity for the first patient will be assessed and used to control for initial group differences in multivariate analyses. We expect each therapist to see ten patients each, with each patient completing up to eight sessions. Fidelity will be assessed only for patients who have attended at least four sessions. Fidelity will be measured for a “midpoint” patient (patient four or five of ten) and the last patient receiving at least four treatment sessions from each therapist. Fidelity for the midpoint and last patient for each therapist is our primary outcome measure. A single overall fidelity rating will be completed for each (midpoint and last) patient’s last three sessions. A minimum of 5 % of the total sessions being analyzed will be randomly selected to be rated by both raters to characterize inter-rater reliability.

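### Patient follow-up is timed from a randomization that patients do not undergo; the 3- and 6-month clock should start at each patient's own baseline

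*Protocol article*

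**What the plan says.** Under Aim 2, Clinical outcomes, the article states: "The clinical status of veterans participating in the study will be assessed at baseline, 3, and 6 months post randomization". The same paragraph adds: "The baseline assessment will be conducted prior to beginning CBT treatment".

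The unit randomized is the provider (Aim 2: hybrid type III study): "Mental health providers will be randomized to receive CBT training plus the CALM tool or a manualized version of CALM". No randomization of patients is described.

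The order of events follows from two other sections. Training and consultation makes part of the training arm-specific ("The training will differ across the two groups (those randomized to receive the CALM tool versus manual"), so allocation is known before training ends. Aim 2, Study participants, brings patients in after that: "Upon completion of training, each mental health provider will invite ten of his/her patients to participate in CBT treatment".

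Fidelity ratings treats each caseload as an ordered series: "We expect each therapist to see ten patients each, with each patient completing up to eight sessions", and "Fidelity will be measured for a “midpoint” patient (patient four or five of ten) and the last patient". It also says that the rated sessions come from early and late in the project.

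The Aim 2 Data analysis section gives the visit schedule a second time, as a baseline followed by 3- and 6-month follow-up. It does not mention randomization and names no other starting point.

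**The concern.** The schedule mixes two clocks. Baseline belongs to the patient; randomization belongs to the provider and comes before every one of that provider's patients has entered. The interval between the two differs from patient to patient.

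If the schedule were run as written, a 3-month score would mean different things for a provider's first and tenth patient: perhaps most of a course of CBT for one, and little or none for the other. Change from baseline to 3 and 6 months would then average over unequal exposure. That weakens the test of the Aim 2 hypothesis that patients of CALM-tool providers do better. It would also tie exposure at assessment to how quickly each provider enrols, which happens after allocation.

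**Working it through.** The article states no figure on this point to reproduce. The related count does agree: 34 providers × 10 patients = 340 veterans, as in Table 1.

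**Inputs from the article:** ten patients per provider, up to eight sessions each, patient entry after training, and assessments at 3 and 6 months after randomization. Three months is 13.04 weeks and six months is 26.09 weeks.

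**Inputs assumed, because the article gives neither:** the lag L from provider randomization to the first patient (0, 4 or 8 weeks) and the gap g between successive patient starts (0 to 8 weeks). I also take baseline to fall at the start of that patient's CBT; the article says only that it comes before it.

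**Formula.** Patient k (k = 1 to 10) starts at week L + g(k − 1). On the literal clock, the 3-month assessment falls at or before baseline if that start is at or after week 13.04, and the 6-month assessment if it is at or after week 26.09.

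Patients out of 10 whose assessment falls at or before baseline (3 months / 6 months):

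| Gap g | L = 0 | L = 4 | L = 8 |
|---|---|---|---|
| 0 weeks | 0 / 0 | 0 / 0 | 0 / 0 |
| 1 week | 0 / 0 | 0 / 0 | 4 / 0 |
| 2 weeks | 3 / 0 | 5 / 0 | 7 / 0 |
| 4 weeks | 6 / 3 | 7 / 4 | 8 / 5 |
| 8 weeks | 8 / 6 | 8 / 7 | 9 / 7 |

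An 8-week gap corresponds to strictly one patient after another with weekly sessions.

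**Thresholds.** The tenth patient is the first to be affected, once L + 9g reaches the visit week.
- 3 months: g = (13.04 − L)/9, which is 1.45 weeks at L = 0 and 0.56 weeks at L = 8.
- 6 months: g = (26.09 − L)/9, which is 2.90 weeks at L = 0 and 2.01 weeks at L = 8.

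**Unequal exposure without any visit before baseline.** The first and tenth patients start 9g weeks apart. Take L = 4 and g = 1, where the table shows 0 / 0:
- The first patient starts at week 4, so the 3-month assessment comes 13.04 − 4 = 9.04 weeks after baseline.
- The tenth starts at week 4 + 9 = 13, so it comes 13.04 − 13 = 0.04 weeks after baseline.

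**With the clock started at the patient's own baseline,** 0 of 10 assessments can fall at or before baseline at either visit, at any pace.

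**The case against.** The best defence is that the phrase is loose wording. The Aim 2 Data analysis section restates the schedule without it, in terms that read most naturally as time from the patient's baseline. Clinical outcomes itself calls the later visits follow-up. Disorder-specific assessment continues only for patients who screened positive at baseline, so a visit before baseline could not be carried out under that rule. This stands as evidence of what was probably intended. It does not settle the matter, because Data analysis names no origin, and the one section that does names one that patients do not have.

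The second defence also stands: the article gives no enrolment pace, no lag and no limit on overlapping patients. Providers may invite all ten soon after training. The ordering into first, midpoint and last patients shows a sequence, but not that one course ends before the next begins.

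Three stronger readings are therefore tempting but unsupported:
- That many 3- and 6-month visits would fall before baseline. The range starts at zero, and at a 2-week gap no 6-month visit is affected at any of the lags tried.
- That the arm comparison is biased. This needs the tool to change enrolment or session pace, and nothing in the article says that it does.
- That the sponsor chose the provider's clock deliberately. Nothing shows this.

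**Conclusion.** The point holds as an error in the stated time origin. Patients are not randomized, so 3 and 6 months after randomization can only refer to the provider's date. On that clock, time since a patient's own baseline varies between patients whenever their starts are staggered; this does not depend on any particular pace.

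The number of assessments at or before baseline does depend on pace: 0 to 9 of 10 patients per provider at 3 months and 0 to 7 of 10 at 6 months, over the assumed lags and gaps. It is zero if all ten start together, or weekly with a lag of up to 4 weeks.

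The consequence is dilution of the secondary patient-outcome comparison, with bias only if enrolment pace differs by arm. The amount of dilution cannot be calculated, because the article gives neither the pace nor the course of response over time. The primary outcome, provider fidelity, is rated from session recordings and does not use this clock.

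**What to change.** In Clinical outcomes, state the schedule as a baseline assessment before the patient's first CBT session, then assessments 3 and 6 months after that patient's own baseline assessment, with the same visit windows in both arms. Word the schedule in the Aim 2 Data analysis section the same way, and use this clock in the secondary analysis.

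The cost is one line in each of the two sections and a setting in the telephone-interview scheduler. No assessments are added.

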### Data analysis

Providers will be the unit of the intent-to-treat analysis for measuring our primary (fidelity to the CBT model) and secondary (mental health) outcomes. For our primary outcomes, the dependent variable will be the composite fidelity score from each provider’s midpoint and last patient. The composite score will be calculated as the mean of the two scores. A dummy variable representing treatment group assignment will be specified as the explanatory variable of interest. An alpha significance level of 0.05 will be used to reject/accept the null hypothesis. Study hypotheses will be tested using a standard logistic regression model. Three covariates will be specified to control for differences across providers. We will first examine differences in the characteristics of providers across the intervention and control group and include those characteristics that differed statistically. If no group differences are observed in the characteristics of the providers, we will control for previous CBT experience (none, some, most experience) and length of time in clinical practice. To examine our secondary outcomes, overall mental health functioning will be measured at baseline and at 3 and 6 months follow-up. Patients will also be screened for any of five specific disorders at baseline (PTSD, PD, GAD, SAD, and comorbid depression); and for those who score positive in a given disorder, ongoing assessment of that disorder will continue through the study. We expect a high degree of comorbidity, so participants will choose the disorder that is bothering them the most as the “target” disorder for CBT treatment.

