### Data collection

#### Fidelity assessments

Fidelity to the CBT model will be the primary outcome. Consistent with the recommendations [39], a multidimensional approach to measuring fidelity will be taken. We will use the fidelity rating scales employed in the prior CALM study in which fidelity is rated on a 1 to 7 scale using multiple items spanning three domains: protocol adherence, protocol competence, and global competence. Although separate ratings will be completed for each of these three domains, they will ultimately be combined to create a single measure of fidelity. We will add a fourth domain (non-adherence) developed just for this study. We believed this additional measure would be useful in identifying incidents of serious non-adherence to the CBT model which is associated with poorer treatment outcomes [40].

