### Power analysis

The power calculation for our *primary outcome* takes into consideration analyses involving comparisons of means and proportions. In making these power calculations, we assume that two therapists in each group (four in total) will either “drop out” of the project, change jobs, or leave VA employment, leaving us with a sample size of 30. With a sample size of *n* = 30 therapists, we will have an 84 % power to detect a large effect size (Cohen’s *d* = 1.0) in mean treatment fidelity based on all sessions from each therapist’s mid and last patients. This calculation assumed a 1.2 point difference in mean fidelity between the intervention and control groups, a pooled standard deviation of 1.2, alpha = 0.5, and a two-tailed test of significance. With a sample size of *n* = 30 providers, we will also have 88 % power to detect a 35 % difference (85 versus 50 %) in the proportion of therapists maintaining minimally acceptable treatment fidelity between the intervention and control groups based on all sessions from each providers mid and last patients. This calculation assumed a 0 % attrition rate, alpha = 0.05, and a two-tailed test of significance.

It will not be necessary for patients to complete a full course (eight sessions) of CBT to be included in the study so we expect minimal “drop out” of patients. The power calculation for our *secondary outcome* must take into account the clustering of patients with providers. Prior psychotherapy RCTs have found intraclass correlation coefficients to vary widely (range 0 to 0.73) with a mean of about 0.08 [41]. We based our power analysis on a slightly conservative intraclass correlation coefficient of 0.10. With a sample size of *n* = 300, we will have 85 % power to detect a medium effect size (Cohen’s *d* = 0.5) for our secondary outcome of overall mental health functioning [42].

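### The primary fidelity outcome is a mean score, but the stated test is a logistic regression, which needs a binary outcome

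*Protocol article*

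**What the plan says.** All references are to the protocol article, Aim 2.

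- **Outcome.** Under Fidelity assessments, "fidelity is rated on a 1 to 7 scale using multiple items spanning three domains", and the domains are combined into one measure. Under Data analysis, "the dependent variable will be the composite fidelity score from each provider’s midpoint and last patient", and "The composite score will be calculated as the mean of the two scores".
- **Test.** The same Data analysis paragraph sets the level ("An alpha significance level of 0.05 will be used to reject/accept the null hypothesis") and names the model: "Study hypotheses will be tested using a standard logistic regression model". Treatment group enters as a dummy variable, with three covariates.
- **Power.** The Power analysis section says that the calculation for the primary outcome "takes into consideration analyses involving comparisons of means and proportions". The first calculation is for means: "This calculation assumed a 1.2 point difference in mean fidelity between the intervention and control groups", with SD 1.2, 30 therapists and a stated power of 84 %. The second is for the share of therapists reaching acceptable fidelity, 85 % versus 50 %, with a stated power of 88 %.

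**The concern.** The dependent variable is a mean of two multi-item ratings, so it takes many values. A standard logistic regression models a yes/no outcome. Within one paragraph the outcome and the model do not fit together, and nothing there converts one into the other.

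Fidelity is the trial's primary outcome, and the Aim 3 section ties support for a national rollout to it. An analyst who follows the text literally has to change either the outcome or the model. If the outcome is changed by cutting the score, information is lost in a sample of only about 30 providers, and some model fits may fail.

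**Working it through.** **Inputs.** 34 providers are recruited and two are lost per group, which leaves 30. Equal allocation, and hence 15 per arm, is inferred. Difference 1.2, SD 1.2, so d = 1.0. Two-sided alpha is taken as 0.05 from Data analysis; the means calculation prints "alpha = 0.5, and a two-tailed test of significance", which is read here as a misprint.

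**1. The plan's own power figures, at 15 per arm.**

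*Means.* The noncentrality is d × √(n/2) = 1.0 × √7.5 = 2.739.
- Normal approximation: Φ(2.739 − 1.960) = 78.2 %.
- Noncentral t, 28 df, critical value 2.048: 75.3 %.

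Neither gives the stated 84 %.

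*Proportions, 85 % versus 50 %.* The pooled rate is 0.675.
- z = [0.35 × √15 − 1.96 × √(2 × 0.675 × 0.325)] / √(0.85 × 0.15 + 0.50 × 0.50) = (1.356 − 1.298) / 0.614 ≈ 0.093, so power is 53.7 %.
- Exact enumeration without covariates: likelihood-ratio test 56.9 %, Wald test 39.1 %.

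The stated 88 % is approached only with about 30 per arm (87.7 %, unpooled formula). The stated figures therefore do not show that the binary version is the better powered one.

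**2. What dichotomising does to the plan's effect.** Take a normal score shifted by 1 SD.
- Cut at the control mean: Φ(1) = 84.1 % versus 50.0 %, close to the plan's 85 % versus 50 %.
- Cut midway between the arm means: Φ(0.5) = 69.1 % versus 30.9 %.

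**3. Linear versus logistic with covariates.** Simulation with 15 per arm, d = 1.0, two-sided 0.05, treatment plus three independent non-prognostic covariates, and failed fits counted as non-significant for the Wald test. Separate runs of 4,000 to 6,000 trials agreed closely.

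| Analysis | Cut at control mean | Cut midway |
|---|---|---|
| Linear regression of the score (no cut) | 70–73 % | 70–73 % |
| Logistic, likelihood-ratio test | about 56 % | about 60 % |
| Logistic, Wald test | about 40 % | about 50–53 % |
| Logistic fits that separate or fail | about 8 % | about 1 % |

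Under no effect (control-mean cut), the likelihood-ratio test rejected in about 7–8 % of trials rather than 5 %, so part of its apparent power comes from excess type I error.

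**4. Why the logistic model is fragile here.** At 85 % versus 50 %, the smaller outcome class is expected to hold 15 × 0.15 + 15 × 0.50 = 9.75 providers. Treatment plus three covariates is four slopes if each covariate takes one term: 9.75 / 4 ≈ 2.4 providers per slope. A three-level experience covariate coded with two terms would lower this further.

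**The case against.** The strongest reply is that this is a wording slip. A mean score, a treatment dummy, covariates and a power calculation on means all point to linear regression, and the printed alpha of 0.5 shows that the text contains other slips. On that reading no power is lost. This may well be right, but the sentence is then wrong as printed and still needs correcting.

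A second reply is that the logistic model was meant for the proportion calculation in the Power analysis section. In that case the defined dependent variable does not match the test, and the mean score has no named model.

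Four stronger readings are tempting and are not supported:

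- **Power is halved.** That is roughly so only for the Wald test with the cut at the control mean. The article names neither a test statistic nor a cut, and the likelihood-ratio test keeps about three-quarters or more of the linear model's power.
- **Separation is a general risk.** The 8 % failure rate belongs to one cut; the other gives about 1 %.
- **The plan allows two tries at 0.05.** Nothing in the article proposes choosing between mean and proportion after seeing the data. It defines one dependent variable.
- **The missing cut-off for acceptable fidelity is itself a fault.** A journal article may leave that to the full protocol or analysis plan.

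**Conclusion.** The mismatch is certain and rests on the text alone: the named primary test cannot be applied to the defined primary outcome, so the sentence must be corrected.

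The power loss is conditional. It arises only if the mismatch is resolved by dichotomising the score. It is then about 10–17 percentage points with the slightly liberal likelihood-ratio test (70–73 % against 56–60 %), and about 17–33 points with the Wald test (70–73 % against 40–53 %).

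These figures assume 15 per arm, normally distributed scores with equal SD, alpha 0.05, and covariates unrelated to fidelity. Covariates that predict fidelity, such as the first-patient score mentioned under Fidelity ratings, could raise power; the article gives no correlation from which to quantify this.

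**What to change.** - In the Aim 2 Data analysis section, replace the logistic model with a linear regression of the composite fidelity score on treatment arm plus the plan's covariates. Report the mean difference with a 95 % interval, and name this as the single primary test.
- In the Power analysis section, state that the comparison of means is the primary one. Keep the proportion with acceptable fidelity as supportive only, analysed with an exact or small-sample method.

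The choice of covariates, including the adjustment for first-patient fidelity, is a separate question and is left unchanged here. The stated powers of 84 % and 88 % should be recalculated when the section is edited.

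The cost is a few sentences in two sections, with no operational change. According to Study status, only Aim 1 focus-group recruitment had begun at submission, so on that timetable the correction could precede any fidelity rating.

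### The primary model's covariates are chosen by significance tests of baseline differences between randomised arms, and the investigators' own default covariates are used only if nothing differs

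*Protocol article*

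**What the plan says.** The rule is in the Protocol article, Aim 2, Data analysis. It opens with a count: "Three covariates will be specified to control for differences across providers". It then gives two branches.

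- Branch 1: "We will first examine differences in the characteristics of providers across the intervention and control group and include those characteristics that differed statistically".
- Branch 2: "If no group differences are observed in the characteristics of the providers", then "we will control for previous CBT experience (none, some, most experience) and length of time in clinical practice".

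The section gives no list of candidate characteristics, no significance level for these comparisons and no limit on how many may enter. Branch 2 names two covariates, not three.

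A separate sentence under Fidelity ratings bears on the same model: "Fidelity for the first patient will be assessed and used to control for initial group differences in multivariate analyses". The Data analysis section does not mention that variable.

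Allocation is by randomisation: "Mental health providers will be randomized to receive CBT training plus the CALM tool or a manualized version of CALM". The trial is small: "We will recruit 34 mental health providers (all disciplines eligible) to receive training in CBT". The Power analysis section expects two losses per group, which leaves 30 providers for analysis.

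**The concern.** Adjusting for a covariate in a randomised comparison helps to the extent that the covariate predicts the outcome. A significance test between arms does not measure that. If randomisation was done properly, the null hypothesis of that test is true by design, so a significant result marks only an unusual draw.

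The test is also blunt at this sample size. A moderate imbalance in a variable that matters for fidelity will usually pass unselected, while a large imbalance in an irrelevant one is let in.

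The two branches add to this. The investigators evidently regard previous CBT experience and time in practice as the variables worth controlling for, since those are their defaults. Yet one chance difference elsewhere is enough to take out whichever of the two did not itself differ.

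At stake are the precision of a single comparison of about 30 providers, and a primary model that cannot be written down before the arms have been compared.

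**Working it through.** **Inputs from the Protocol article.** 34 providers recruited, 30 analysed (Power analysis); equal arms of 15 assumed. Target effect d = 1.0 (difference 1.2, SD 1.2). Analysis alpha 0.05 (Data analysis).

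**Inputs assumed.** Baseline tests at 0.05 (level not stated); 2 to 10 independent characteristics tested (number not stated); the two defaults jointly explain a share R2 of fidelity variance of 0.1 to 0.4 (not stated).

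**The plan's own figure.** The plan gives none for this rule. The nearest is its 84 % power for d = 1.0. With 15 per arm and a two-sided 0.05 test, I get 78.2 % (normal approximation) or 75.3 % (t-test). That mismatch is a separate matter; here 75.3 % serves only as the unadjusted reference.

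**Step 1: imbalance needed for selection.**
t(0.975, 28) × √(2/15) = 2.048 × 0.365 = 0.75 SD. An imbalance of 0.5 SD would not be selected.

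**Step 2: chance that branch 1 is triggered.** For k independent characteristics this is 1 − 0.95^k:

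- k = 2: 9.8 %
- k = 5: 22.6 %
- k = 6: 26.5 %
- k = 10: 40.1 %

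**Step 3: price of admitting an irrelevant but unbalanced covariate.** Adjusting for one covariate whose between-arm t statistic is t multiplies the variance of the treatment estimate by 1 + t²/28. At the selection threshold this is 1 + 2.048²/28 = 1.15. A selected covariate unrelated to fidelity therefore costs at least about 15 % in variance and returns nothing.

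**Step 4: power at d = 1.0.** Simulation with 15 per arm, a linear model, and the two defaults among the characteristics tested; 12,000 runs per setting for 5 or 10 tested, 4,000 for 4 or 6.

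| Joint R2 | Tested | Plan's rule | Defaults always in | Loss (points) |
|---|---|---|---|---|
| 0.1 | 4 | 75 % | 76 % | 1 |
| 0.1 | 6 | 74 % | 76 % | 2 |
| 0.2 | 5 | 79.1 % | 81.5 % | 2.4 |
| 0.2 | 10 | 76.0 % | 81.3 % | 5.3 |
| 0.3 | 6 | 82 % | 86 % | 4 |
| 0.4 | 5 | 87.8 % | 91.9 % | 4.1 |
| 0.4 | 10 | 81.3 % | 90.3 % | 9.0 |

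The unadjusted analysis gave 75 % to 76 % in the 12,000-run settings, in line with the 75.3 % above.

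**Step 5: the trials in which branch 1 is triggered.** In the four 12,000-run settings, power in these trials was 67 % to 73 % under the rule and 79 % to 92 % with the defaults fixed. The unadjusted analysis gave 74 % to 75 %, so once triggered the rule did worse than no adjustment. At least one default was dropped in about 22 % to 23 % of trials with 5 characteristics tested and about 40 % with 10.

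**Step 6: false positives.** With no true effect, the rule rejected in 4.5 % to 5.1 % of trials.

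**The case against.** **First-patient fidelity is adjusted for regardless.** The Fidelity ratings section says so without condition, and an early measure of the same outcome may well predict later fidelity better than either default. It could also be the missing third covariate. This stands in part. If such a variable is always in the model, less is lost: with an assumed R2 of 0.3 for it and 0.1 for the defaults, power is 88 % against 90 % (four tested) or 87 % against 89 % (six tested). With 0.4 and 0.05 and four tested, it is 91.0 % against 91.4 %. A reader should therefore not infer that all useful adjustment disappears when branch 1 is triggered. But the Data analysis section gives this variable no place in the model. It is also measured after randomised training whose last two hours each day differ by arm, so it can carry part of the treatment effect and is not a true baseline covariate.

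**The defaults are not shown to be prognostic.** Correct. One might infer that the rule throws out known predictors of fidelity, but the article names the two only as defaults and cites no evidence for them. Nor are both always lost, since a default that itself differs is kept.

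**The power loss rests on assumptions.** Also correct. The number tested and the R2 are not in the article. The simulation uses a linear model because the outcome is a mean score, whereas the article names logistic regression, which is a separate question. The loss is therefore given only as a range.

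**The rule usually beats no adjustment.** Overall, yes, when the defaults predict fidelity at all well. The relevant comparison, though, is with fixing the same two covariates in advance, which asks for no new variable.

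**Conclusion.** The point holds as a should-fix. The article itself states the rule, so this is not detail left to an analysis plan. Selection by baseline significance test leaves the primary model unknown until the arms are compared, and a chance difference elsewhere displaces one or both defaults.

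The chance of triggering is about 10 % for 2 independent characteristics, 26 % for 6 and 40 % for 10. The power loss at d = 1.0 is roughly 1 to 10 points overall (linear model, joint R2 of 0.1 to 0.4, 4 to 10 tested). It is larger in the trials where the rule is triggered, and smaller if another strong predictor is always in the model.

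A reader might infer that choosing the model after looking at the arms inflates the false-positive rate. The calculations do not support that: the choice uses baseline characteristics and not the outcome, and rejection under the null stayed near 5 %. The harm is lost precision and a model not fixed in advance.

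**What to change.** 1. Delete the baseline tests and the two-branch rule. State that the primary model adjusts in every case for previous CBT experience (three levels) and length of time in clinical practice, both recorded before randomisation, whatever their observed balance.
2. Report other provider characteristics by arm descriptively, without p-values.
3. Reconcile the stated three covariates with the two named: name the third or correct the count.
4. State whether first-patient fidelity is in the primary model. If it is, acknowledge that it is measured after training that differs by arm, so that adjusting for it may remove part of the effect being estimated.

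**Cost.** This is a wording change in the protocol and any analysis plan, plus making sure the two covariates are recorded before randomisation; the article does not say when they are collected.

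The statistical price is up to three degrees of freedom in every analysis (two for experience, one for time in practice). With 30 providers, three unrelated covariates raise the variance of the treatment estimate by a factor of about 27/24 = 1.125 on average (approximately normal covariates). Relative to no adjustment, the covariates pay for themselves once they explain about 1 − 1/1.125 = 11 % of the variance; below that there is a slight loss. The plan's own branch 2 already accepts this price.
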